## Abstract

**Background:**

Depression, anxiety and work-related stress affect a significant number of adults disrupting their productivity, ability to function and attend work. These highly comorbid disorders tend to be difficult to treat effectively, and more information about integrative treatment approaches is needed. This study investigates the effectiveness of music therapy in treating depression-related disorders.

**Methods/design:**

The intervention is targeted at people of 18–65 years of age who are in employment, in their studies, temporarily unemployed, on short-term sick leave or rehabilitation allowance and suffer from depression-related disorders, which include one or several of the following: depression, anxiety, work-related stress or exhaustion. The interventions applied are Integrative Improvisational Music Therapy (IIMT) with or without the additional elements of music listening and vibroacoustic treatment. All sessions will begin with a preparative exercise called Resonance Frequency Breathing to enhance the effect of the therapy. All participants will receive the intervention for 6 weeks (60-min therapy session twice a week). The participants will be randomised into four groups that will have different modifications of the intervention, and the group without additional elements will serve as a waiting-list control group. The primary outcome will measure psychological distress. Secondary outcomes will address depression, anxiety, exhaustion, burnout, health-related quality of life and challenges in recognising emotions (alexithymia).

**Discussion:**

The trial will elevate our understanding of the efficacy of integrative improvisational music therapy for depression-related disorders. Results will give more information about the combinations of additional elements used as part of the intervention. Extensive dataset will allow us to investigate the dynamics of therapeutic change and the factors that predict certain responsiveness to the intervention or explain the effects.

**Trial registration:**

Prospectively registered on ISRCTN on 12.04.2024 (ISRCTN26812986). Study was approved by the Regional Medical Research Ethics Committee of Wellbeing Services County of Central Finland 15.02.2024 (ref: 7U/2023).

**Supplementary Information:**

The online version contains supplementary material available at https://doi.org/10.1186/s13063-026-09864-4.

## Introduction

### Background and rationale {6a}

Depressive, anxiety and exhaustion disorders affect a significant proportion of adults [1, 2]. These disorders disrupt an individual’s ability to function normally, lead to reduced productivity, heightened work absenteeism, and more frequent medical consultations. Although various treatment options are available, the comorbid nature and varied presentation of these disorders make them difficult to treat effectively. Thus, an integrative approach that is tailored to the individual is essential. In this study, we propose Integrative Improvisational Music Therapy (IIMT) [3] as one such method and will study its efficacy in different variations.

According to the Finnish Institute for Health and Welfare [4] depressive disorders are the most common mental health conditions and a major public health issue affecting working age individuals in Finland. They are characterized by feelings of sadness and hopelessness and a loss of pleasure or interest in activities. Physical symptoms like loss of appetite and excessive sleep are also associated with them [5]. Their prevalence among Finnish adults is estimated at 5–7%, and both their personal and societal burden are significant [6]. They are the single largest cause for disability pension in Finland [4].

Anxiety disorders are another common mental health condition in Finland. They are characterised by excessive fear and worry not only about specific but also everyday situations. Physical symptoms can include sweating, trembling, shaking; experiencing abdominal pain or nausea; and having difficulties concentrating and performing other cognitive tasks [7]. The prevalence of anxiety disorders is more difficult to estimate, as they are highly comorbid with other mental disorders and often remain undiagnosed. However, population-based surveys suggest that the lifetime prevalence of anxiety disorders among adults aged 18 to 64 is 6.6% [8]. Anxiety and depressive disorders are often comorbid. A survey by Kessler et al. [9] reported that 47.5% of individuals who had experienced major depressive disorder at some point in their lives also had a lifetime history of one or more anxiety disorders. The comorbidity of depression and anxiety is due to the overlap of symptoms and the shared structural and functional pathways of changes in the brain that are associated with these disorders [10].

Another condition called exhaustion disorder may develop as a result of prolonged stress [11]. It is characterised by physical and emotional fatigue often resulting from work-related stress. While depression and anxiety are classified as disorders by the Diagnostic and Statistical Manual of Mental Disorders (DSM), exhaustion is not. Thus, according to Finnish Current Care Guidelines, exhaustion is currently not recognised as a separate disorder in Finland, which complicates the process of seeking and receiving treatment. However, research conducted in Sweden found that fatigue was inadequately addressed by adjustment disorder, an existing stress-related diagnosis. As a result, they proposed provisional criteria for a new condition called ‘exhaustion disorder’. Conceptually akin to the construct of burnout, exhaustion disorder was incorporated into the Swedish version of the International Classification of Diseases (ICD-10) in 2005, classified under F43.8A Reaction to severe stress. Since its introduction, the diagnosis of exhaustion disorder is almost as prevalent as that of major depression in Swedish healthcare settings [2].

The terms ‘exhaustion disorder’ and ‘burnout’ are often used interchangeably and in this study, we will treat them as the same condition. In a report by de Hert [12], the prevalence of burnout in the European Union countries ranges from 4,3% in Finland to 20,6% in Slovenia. The study also indicated that an increase in workload correlates positively with burnout. According to Finnish Institute of Occupational Health [13] approximately one in four Finns have an increased risk for occupational burnout and severe burnout concerned 10% of people in 2024. These people experience symptoms of burnout constantly but may still be at work. While exhaustion disorder has distinct symptoms, individuals affected by it have reported higher levels of anxiety and depression, often meeting the criteria for both conditions simultaneously [2, 14].

Thus, depressive symptoms are common in all these conditions: in anxiety, due to its comorbid relationship with depression [15] and in exhaustion, as many of the symptoms of exhaustion disorder overlap with that of major depressive disorder [16]. The relationship between depression, anxiety, exhaustion exist not only through aetiology and pathophysiology but also because treatment practices used for classified disorders (depression, anxiety) are used for treating non-classified disorders (exhaustion) as well.

While pharmacological treatments can be effective in treating conditions with a clear diagnosis, they are not as effective in treating conditions with complex comorbidities. Additionally, the use of antidepressants (the most commonly prescribed pharmacological treatment for depression) is associated with a variety of side effects which are often underreported in clinical trials [17]. Hence, more integrated treatment approaches incorporating psychosocial support also need to be adopted that not only alleviate the symptoms of the disorder but also do not cause any harm.

In Finland, depression is usually treated with psychotherapy that has proven to be effective, with medication or with a combination of the two [6]. According to the Current Care Guidelines, these treatments are equally effective for mild and moderate depression, and their simultaneous use often yields the best outcomes. As much as pharmacological treatments provide symptomatic relief, psychotherapy helps clients understand the root causes of their symptoms, process their emotions and provide coping strategies which enhance long term wellbeing.

Music therapy is one form of psychotherapy that can be used to treat and manage depression and other mental health conditions [18]. It uses music to facilitate non-verbal expression in clients who may struggle to express themselves verbally. It is relaxing, creatively engaging, and is associated with less social stigma [19, 20]. There are two Cochrane reviews on the effect of music therapy for depression [21, 22] with promising findings.

At the University of Jyväskylä (JYU), we have conducted two RCTs on the effect of music therapy on depression in adults [23, 24]. Both were based on the clinical model of Integrative Improvisational Music Therapy (IIMT) which involves active music making through musical improvisation to facilitate self-expression in clients. In IIMT, two musical instruments – a djembe drum and a piano – are used, with both the client and therapist each having their own. All musical expression and interaction take place using these instruments, and is based on clinical improvisation, meaning the client does not need any previous musical experience or specific skills. In addition to clinical improvisation, verbal dialogue plays an important role in the process. Conversations can introduce personal themes and experiences that are then further explored musically, while improvisation can elicit emotions, memories, and associations that are further processed through verbal reflection. This turn-taking between improvisation and verbal processing forms a dialogue in which both modes of expression enrich one another. In this way, the therapeutic process becomes more dynamic and productive. The principles and theory of the IIMT have been described by Erkkilä et al. [3].

In this study, we aim to evaluate the effectiveness of music therapy in alleviating symptoms of depression, anxiety, and exhaustion among individuals of working age. Both previously conducted RCTs showed significant improvement on several outcomes measured, including scores of depression and anxiety. The clinical model of IIMT will be used in the current study as well. Specifically, we will assess the impact of two additional elements to the current IIMT model: music listening (ML) and vibroacoustic treatment (VAT). Participants with symptoms related to depression, anxiety, and/or exhaustion disorder will be recruited and randomly allocated to one of four conditions: (A) a waiting-list control group, which will receive standard IIMT after the waiting-list period; (B) ML + IIMT; (C) VAT + IIMT; and (D) VAT + ML + IIMT. Measures of psychological distress, depression, anxiety, and exhaustion will be collected before and after the intervention, as well as in follow-ups at 6-month and 12-month timepoints.

## Objectives {7}

The aim of the study is to focus on depression and anxiety symptoms of individuals of working age and to expand the scope to cover exhaustion as well. This RCT’s intervention is targeted at adult individuals who are in employment, in their studies, temporarily unemployed, on short-term sick leave or rehabilitation allowance and have one or various of the following disorders or conditions: depression, anxiety, work-related stress or exhaustion.

Objective 1: To examine whether IIMT, offered in four different modifications, improves the participants’ condition relative to the control/TAU (Treatment as usual) group. We also aim to find out whether any of the modifications of the IIMT are more effective than plain IIMT.

Objective 2: To understand whether certain musical responsiveness or personality profile explains a client’s improvement in music therapy.

Objective 3: To increase the understanding of the dynamics of therapeutic change by IIMT in its original form and with selected modifications.

Objective 4: To increase the understanding of the essence, mechanisms and trajectories of work-related stress and burnout and their relationship to depression and anxiety.

Hypothesis 1: All the experiment groups (ML + IIMT, VAT + IIMT, VAT + ML + IIMT) improve significantly relative to the control/TAU group.

Hypothesis 2: ML + IIMT group improves significantly better than the IIMT only group.

Hypothesis 3: VAT + IIMT group improves significantly better than the IIMT only group.

Hypothesis 4: VAT + ML + IIMT group improves significantly better than ML + IIMT, and VAT + IIMT groups.

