## Trial design {8}

The study is a randomised 2 × 2 factorial trial, using four conditions: IIMT, IIMT with an additional component of music listening (ML), IIMT with an additional component of vibroacoustic treatment (VAT), and IIMT with the additional elements of both ML and VAT. A superiority design is adopted with the aim of testing whether the intervention, in different conditions, demonstrates statistically and clinically superior outcomes compared with the comparator.

All sessions regardless of the condition will begin with a preparing exercise called Resonance Frequency Breathing (RFB) [24]. There will be a waiting-list control group to whom the plain IIMT will be offered after six weeks of baseline measurements, allowing a within-subject comparison between baseline and treatment conditions. Each group is offered a therapy process consisting of 12 sessions, conducted twice a week for 60 min each.

Outcomes will be measured before and after the start of the therapy and at two follow up points, 6 months and 12 months after the start of the therapy. For Condition A there will be additional baseline 2 measurements before the start of the therapy (see Fig. 1).

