#### Sample size {14}

We will recruit 200 working-age adults (18–65 years of age) suffering from one or several of the following disorders: depression (ICD-10: F32 or F33), anxiety (ICD-10: F41), or exhaustion. The sample of participants will be randomised into four groups (50 + 50 + 50 + 50) of which two groups (*n* = 100) will receive vibroacoustic treatment (VAT) and two groups (*n* = 100) not whereas two groups (*n* = 100) will receive music listening (ML) and two groups (*n* = 100) not (see Table 2).

**Table 2 Tab2:** Factorial design

	VAT yes	VAT no	
ML yes	50	50	*n* = 100
ML no	50	50	*n* = 100
	*n* = 100	*n* = 100	

For each condition, the selected sample size provided a statistical power of 0.985 for detecting a medium standardised effect size of Cohen’s d = 0.5 in a mixed-model analysis [47], with a 2-tailed significance level of *p* < 0.05 and intra-participant correlation of ρ = 0.6. For the comparison between IIMT only vs waiting-list control, the selected sample size provided statistical power of 0.9 for detecting a medium effect size (d = 0.23) in a repeated measures t-test, with a 2-tailed significance level of *p* < 0.05. These high-power levels ensure a robust detection of clinically meaningful effects, even after accounting for potential participant dropouts, while reducing the likelihood of Type II errors. Also, the selected sample sizes also retain adequate power (> 0.8) to detect smaller effects (e.g., d = 0.2), thus providing sensitivity to subtle group differences.

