## Statistical methods

### Statistical methods for primary and secondary outcomes {20a}

All statistical tests will be two-tailed with a significance level of 5%, and no adjustments will be made for multiplicity. Primary and secondary outcome measures at baseline, post-intervention, and at the first and second follow-ups will be treated as continuous dependent variables.

For the IIMT group, which also serves as the waiting-list control, we will assess clinical improvement by comparing their progress during the intervention period with that observed during the waiting period prior to treatment. Specifically, we will perform paired samples t-tests for each outcome measure, comparing the change from baseline 2 (6 weeks; pre-intervention) to post-intervention (12 weeks) against the change from baseline 1 (0 weeks; no intervention) to baseline 2 (6 weeks). Prior to analysis, we will assess the normality of the difference scores to ensure the assumptions of the t-test are met. This comparison will help isolate the treatment effect from natural fluctuations over time.

Since the participants are randomised either to the waiting list plus plain IIMT group or to one of the other three arms (B, C, and D), comparisons between plain IIMT and the waiting list are based on within-subject analyses rather than fully randomised group contrasts. No direct comparisons between the waiting list group and arms B, C, and D will be performed.

To evaluate the effects of VAT and ML on these outcomes, repeated-measures linear mixed-effects models will be applied [50]. A key advantage of this design is its ability to retain participants with missing data, ensuring that all participants contribute to the analysis. Additionally, they can account for baseline group differences, to avoid overestimating the effect size of treatment. VAT and ML will be included as fixed effects, with a random intercept for each participant to account for the dependency of repeated measurements. To control for baseline differences across conditions, treatment terms will be omitted from the model, allowing the effects of VAT and ML to be estimated through their interactions with time. As an exploratory analysis, the models will be extended to include a VAT × ML interaction term to examine potential synergistic effects between the two interventions.

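### Objective 1 asks whether any modification beats plain IIMT, but the combined arm has no such hypothesis and none of the arm-level comparisons with plain IIMT is a named analysis

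*Protocol article*

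**What the plan says.** **Question.** Objectives {7}, Objective 1, asks "whether any of the modifications of the IIMT are more effective than plain IIMT". Under Interventions, three conditions modify plain IIMT (A): B adds ML, C adds VAT and D adds both.

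**Hypotheses (same section).**
- Hypothesis 1: "All the experiment groups (ML + IIMT, VAT + IIMT, VAT + ML + IIMT) improve significantly relative to the control/TAU group".
- Hypothesis 2 (B v A): "ML + IIMT group improves significantly better than the IIMT only group".
- Hypothesis 3 (C v A): "VAT + IIMT group improves significantly better than the IIMT only group".
- Hypothesis 4 (D v B and D v C): "VAT + ML + IIMT group improves significantly better than ML + IIMT, and VAT + IIMT groups".

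**Design.** Trial design {8}: "The study is a randomised 2 × 2 factorial trial, using four conditions". Sample size {14} has participants "randomised into four groups (50 + 50 + 50 + 50"), which is 100 against 100 for each factor.

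**Analysis.** Statistical methods {20a}: "To evaluate the effects of VAT and ML on these outcomes, repeated-measures linear mixed-effects models will be applied". The two effects are estimated through their interactions with time, and the VAT × ML term enters only in an exploratory extension. The overall effect over time is defined as presence against absence of each factor, and the responder tests are run for VAT and for ML separately. The section also rules out direct comparison of the waiting list with arms B, C and D.

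**The concern.** The objective and the hypotheses are written about arms, while the analysis is written about factors. D against plain IIMT is the one comparison within Objective 1 that lacks a hypothesis as well as a named analysis. Hypothesis 1 does not supply it: its comparator is control/TAU, and the analysis section excludes that comparison for B, C and D.

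The mismatch matters because a factor effect averages over the levels of the other factor. It equals the gain of one modification over plain IIMT only if the two add-ons do not interact. The protocol gives no grounds for assuming that. Arm D delivers both elements within one component of the same recommended 15 minutes as ML alone in B or VAT alone in C, so a combined effect smaller than the sum is plausible. At stake is whether the planned results answer the question that the trial sets itself. A contrast of D with A first named after the data are seen would be post hoc.

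**Working it through.** **1. Hypotheses against analyses**

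| Comparison | Hypothesis | Named analysis |
|---|---|---|
| B v A | 2 | none |
| C v A | 3 | none |
| D v B, D v C | 4 | none |
| D v A | none | none |
| VAT present v absent | none | main model, responder test |
| ML present v absent | none | main model, responder test |

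**2. What a factor effect estimates.** With arm means A, B, C, D:
- ML effect = [(B − A) + (D − C)]/2
- VAT effect = [(C − A) + (D − B)]/2

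Under additivity D − C = B − A, so the ML effect equals B − A. Otherwise it does not. Take B = C = D = A + 0.3. The ML effect is (0.3 + 0)/2 = 0.15, and so is the VAT effect. Each is half the true gain of every modification over plain IIMT.

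The sum of the two factor effects is [(B + D − A − C) + (C + D − A − B)]/2 = D − A. In balanced, complete data this holds with or without interaction. B − A and C − A have no such shortcut; without additivity they need the interaction term.

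**3. Reproducing the plan's power.** Inputs from Sample size {14}: d = 0.5, ρ = 0.6, two-sided 5%, 50 per arm. Assumed: the outcome is the mean of the three post-baseline visits, with no dropout (no rate is given).
- Variance of the mean = (1 + 2 × 0.6)/3 = 0.733
- SE of a factor effect = √(2 × 0.733/100) = 0.121
- SE of an arm contrast = √(2 × 0.733/50) = 0.171
- Power = Φ(effect/SE − 1.96)

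For a factor effect of 0.5 this gives 0.985, the stated figure; for a 50 v 50 contrast it gives 0.83. The match does not identify the formula uniquely: a 50 v 50 comparison of three post values adjusted for baseline gives 0.984.

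**4. Power of the contrasts on the same assumptions**

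| True effects (ML, VAT) | ML factor effect | B v A | D v A |
|---|---|---|---|
| 0.20, 0.20, additive | 0.38 | 0.21 | 0.65 |
| 0.25, 0.25, additive | 0.54 | 0.31 | 0.83 |
| 0.5, 0 (one inert) | 0.985 | 0.83 | 0.83 |
| B = C = D = A + 0.3 | 0.24 | 0.42 | 0.42 |

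At 0.25 each, at least one of the two factor tests succeeds with probability 1 − (1 − 0.54)² = 0.79, unadjusted as the plan specifies.

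Under additivity, D v A beats the stronger factor effect only if (a + b)/0.171 > a/0.121, where a is the stronger and b the weaker effect. That means b/a > √2 − 1, about 0.41.

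**The case against.** **The planned model already carries the contrast.** Arms A and D are both in it, and D minus A is the sum of the two factor coefficients. Its variance in units of the outcome variance is 0.02 + 0.02 = 0.04 = 2/50, the same as for a direct comparison. Contrast lists are also commonly left to a statistical analysis plan, which is not shown. This stands in part: nothing new has to be collected or modelled. But the protocol lists its hypotheses and leaves out one that its own objective needs, and what it does specify for the main analysis is at factor level.

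**Hypotheses 2 and 4 together imply D > B > A.** This is true as logic, but it is a weak route. With additive effects of 0.25, both links (D v B and B v A) are significant in only about 4% of trials.

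**A reader might infer that the best-powered test has been left out.** The documents do not support this. The advantage of D minus A needs effects that are similar in size and close to additive, and nothing in the protocol supports either. With one inert add-on the planned factor test is stronger (0.985 against 0.83). If the add-ons cancelled, so that D = A, there would be nothing to find. The advantage at 0.25 each also narrows when error is shared. If B minus A, C minus A and D minus A split the 5% equally, D minus A has 0.70, against 0.67 for at least one of two factor tests at 2.5% each.

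**A reader might also infer that the trial would report no modification as superior when one is.** Simulated on the assumptions above, both factor tests and all the Hypothesis 2 to 4 contrasts miss while D minus A is significant in about 5% of trials at 0.25 each, and in about 0% at the planned 0.5. That is too rare to be the reason for the change.

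**Conclusion.** The point holds as a mismatch between the question and the analysis. Followed as written, the plan gives no stated answer on whether D beats plain IIMT, and no named analysis for the arm-level comparisons in Hypotheses 2 to 4. The bias from reading factor effects as gains over plain IIMT depends on the interaction: none under additivity, and one half (0.15 for 0.3) in the example where the combination adds nothing to either element alone. That example illustrates the size; it is not a prediction.

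The power figures rest on three averaged visits, ρ = 0.6 and no dropout. They show that D minus A can be stronger or weaker than a factor test, so the case for naming it is that Objective 1 asks for it, not that it has more power. Recruitment is expected to run to the end of 2028 and no interim analysis is planned, so the contrasts can still be pre-specified.

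**What to change.** 1. In Objectives {7}, add the hypothesis that VAT + ML + IIMT improves more than IIMT only.
2. In Statistical methods {20a}, keep the VAT and ML factor effects as the main analysis. Add that, for CORE-OM, B minus A, C minus A and D minus A, and D minus B and D minus C for Hypothesis 4, are estimated with 95% confidence intervals as linear combinations from the model with VAT, ML and VAT × ML by time.
3. State the status of these contrasts relative to the factor effects, because the interaction model is now labelled exploratory, and say which result answers each hypothesis.

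The cost is a few sentences and contrasts from a model that is already planned; no new data are needed. The downside is more comparisons on the primary outcome, in a plan that makes no multiplicity adjustment, and lower precision than the factor effects (standard error 0.171 against 0.121 on the assumptions above).
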